### Recruitment {15}

Potential participants will be identified and sought from three main sources: existing AAA registries, collaborating hospitals and vascular departments and community sources and collaborations. We will also work with every site to explore other databases held by imaging services and research groups.

#### Registry recruitment

Previous trials demonstrate that registry-based recruitment methods can facilitate the recruitment of many thousands of participants over short periods of time in a cost-effective manner [44]. Study invitation packages, including a letter of invitation (LOI), study brochure and a postage-paid return envelope, will be mailed out to potentially eligible individuals. About 7–10 days after mailing the study invitation or on receipt of a returned and completed LOI (except when a LOI indicates an individual does not want to be contacted), a staff member will call the individual to confirm interest in study participation, assess potential eligibility and answer any questions they may have about the trial. Suitable and interested participants will be consented and enter screening.

#### Collaborating hospitals and vascular departments

Sites that do not have existing AAA registries may identify lists of patients who have an AAA, no prior repair and no diabetes using locally approved methods. This may include identifying patients from vascular laboratory records and electronic medical records. Potential participants may also be identified during routine follow-up with their specialist. Site staff will invite potential participants to the study either in person, by phone or by mail using a combination of the study brochure and LOI. Potential participants who are interested will be consented by appropriately delegated staff and enter screening. For sites that do not have study personnel available, and with appropriate regulatory approvals, and if required participant consent, the collaborating hospitals will provide the coordinating centre with the contact details of potential participants via a secure Web-based system. A study staff member at the coordinating centre will then invite the participants to take part in the study.

#### Community sources and collaborations

To complement these recruitment methods, private medical and surgical centres, general practitioners and practice nurses will also be able to offer a study invitation pack to potential participants when they are seen for routine care in their clinic, or by mail. In addition, investigators will approach large health organisations to promote the study and provide information about how health professionals can help their eligible patients join the study. Lastly, recruited participants will be able to recommend friends or relatives who they think may be eligible and interested in taking part in the study and other potential participants may volunteer themselves if they hear about the study from other sources, such as approved advertisements or the coordinating centre website regarding the trial.

### Assignment of interventions: allocation

#### Sequence generation {16a}

A random sequence for study arm allocation will be generated by the trial statistician prior to commencement. Randomisation will be conducted using a secure Web-based system and will be stratified by study centre, sex and AAA diameter (35–38.9, 39–42.9, 43–46.9 and ≥ 47 mm) on imaging. Randomisation will be blocked in a 1:1 ratio.

#### Concealment mechanism {16b}

The trial statistician will also generate a sequence of unique codes for every active/placebo drug kit. The drug kit codes will be provided to the approved Investigational Medicinal Product (IMP) manufacturer who will ensure that study drug and placebo packs are labelled appropriately and that the study team, pharmacy staff, investigators and participants are blinded to treatment allocation.

#### Implementation {16c}

Each drug kit will contain a 6-month supply of study medication and will be identified by a kit number only. Study medication will be dispensed by the study pharmacist at baseline and 6 monthly thereafter. The kit numbers allocated to participants will be revealed to the study pharmacist on entry of the participant’s ID into the online database management system. For each participant, a new kit code will be generated every 6 months that will correspond with the treatment group the participant has been allocated.

### Assignment of interventions: blinding

#### Who will be blinded? {17a}

All study team members and participants will be blinded to the allocation. The IMP manufacturer will be unblinded to allocation and will generate active drug and placebo which will be identical in appearance and will be concealed by identical packaging, labelling and administration scheduling.

#### Procedure for unblinding if needed {17b}

Emergency unblinding can take place at any time using the secure Web-based system. It will occur for any participant experiencing a serious adverse event (SAE) for which the clinical management of the SAE will be facilitated by the unblinding of the participant’s treatment allocation. The principal investigator will make this decision. It is anticipated that for the majority of instances, appropriate clinical management can proceed with the assumption that the participant has been treated with metformin without needing to unblind the participant. The main reason for unblinding will be in the case of a suspected unexpected serious adverse reaction (SUSAR).

### Data collection and management

#### Plans for assessment and collection of outcomes {18a}

All data will be collected by members of the study team as described in the delegation log. During screening and follow-up, information that is obtained directly from participants may be confirmed from retrospective sources including medical records. In the case of safety monitoring and reporting, confirmation will again be sought about participants’ health status from medical records. All clinical and laboratory-related information will be recorded in a de-identified format using the participant’s unique trial identifier.

The quality of life questionnaires (SF-36 and AneurysmDQoL) have been validated for use in AAA patients. The SF-36 has the advantage of being able to be converted to the SF-6D for a cost-utility analysis [45]. The AneurysmDQoL is an individualised measure of the impact of AAA on patients’ quality of life, containing 23 domains with two overview items to assess the overall quality of life and impact of AAA on quality of life [46].

Source documents for the study constitute consent forms, electronic case report forms (eCRF), information obtained on reported outcome measures, death certificates, pathology results, DICOM ultrasound images and imaging reports and drug supply records. These will be retained for at least 15 years from the completion of the study.

#### Plans to promote participant retention and complete follow-up {18b}

Participants that discontinue study medication will be encouraged to remain on the study protocol, and with their consent, continue to be followed and their data included in the final analysis in accordance with an ITT analysis.

#### Data management {19}

All study data collected for outcome analysis will be completed via a secure password-protected Web-based data management system hosted by IBM Corp, USA. This will allow for real-time data query generation for values entered outside of pre-set valid ranges and consistency checking. This system will facilitate data reporting and assist overall trial management for all participating centres. Data entry will be performed at participating sites, with the exception of sites that do not have study personnel available. In this case, data will be entered by the coordinating centre. Only authorised staff will have access. All entered data forms will be electronically signed by authorised study staff. All changes made following the initial entry will have an electronically dated audit trail. Centralised coding of outcomes will be performed by a trained medical coder and reviewed by the monitor, to confirm the accuracy of coding and correct reporting of outcomes by sites.

#### Confidentiality {27}

Every precaution will be taken to respect the privacy of participants in the conduct of the study. Only de-identified data will be entered into the secure Web-based data management system to maintain participant confidentiality. All individual and site information will be de-identified in reporting data and results to protect the confidentiality of participants. Only approved investigators will have access to data.

#### Plans for collection, laboratory evaluation and storage of biological specimens for genetic or molecular analysis in this trial/future use {33}

A sub-set of participants may consent to the MAT biomarker sub-study which involves exploratory biomarker analysis. Individuals who consent to take part in the additional sub-study will be required to have 20 ml of blood taken including EDTA plasma, citrate plasma, PAX Gene tube, serum and whole blood. Samples will then undergo cooling, centrifugation, separation into cryovials and storage at below −80 °C. These samples will be used to assess relevant biomarkers including D-dimer, matrix metalloproteinases, osteoprotegerin and osteopontin. Samples will be collected at entry, at years 1 and 3 and at the final scheduled follow-up.

#### Additional consent provisions for collection and use of participant data and biological specimens {26b}

A sub-set of participants from sites with resource for blood sampling may consent to the MAT biomarker sub-study which involves exploratory biomarker analysis. Individuals who consent to take part in the additional sub-study will be required to donate 20 ml of blood (including EDTA plasma, citrate plasma, samples for RNA analysis (PAX Gene tube, Qiagen), serum and whole blood). Samples will then undergo cooling, centrifugation, separation into cryovials and storage at below −80 °C. These samples will be used to assess biomarkers relevant to AAA progression including D-dimer, matrix metalloproteinases, osteoprotegerin and osteopontin. Samples will be collected at entry, at years 1 and 3 and at the final scheduled follow-up.

### Statistical methods

#### Statistical methods for primary and secondary outcomes {20a}

All participants who have been randomised will be included in the primary analysis and will be analysed according to their randomly allocated treatment [47]. Statistical analyses will be conducted according to a detailed pre-specified data analysis plan which will be developed prior to completion of the trial and unblinding of data. A brief account of the statistical methods is included here. For the primary outcome, a time-to-event analysis will be conducted to test our hypothesis that metformin will reduce the primary endpoint. The hazard ratio (HR) and 95% CI will be calculated using the Cox proportional hazard analysis, and event risk will be plotted on a Kaplan-Meier graph. A *p*-value < 0.05 will be considered significant. The focus of the trial will be on the primary hypothesis, but we will also examine the effect of metformin on secondary and tertiary outcomes. A detailed statistical analysis plan will be prepared before completion of the trial.

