**Methods:**

MAT is an international, multi-centre, prospective, parallel-group, randomised, placebo-controlled trial. Participants must have an asymptomatic AAA measuring at least 35 mm in maximum diameter, no diabetes, no contraindication to metformin and no current plans for surgical repair. The double-blind period is preceded by a 6-week, single-blind, active run-in phase in which all potential participants receive metformin. Only patients tolerating metformin by taking at least 80% of allocated medication will enter the trial and be randomised to 1500 mg of metformin XR or an identical placebo. The primary outcome is the proportion of AAA events defined as rupture-related mortality or need for surgical repair. Secondary outcomes include AAA growth, major adverse cardiovascular events and health-related quality of life. In order to test if metformin reduced the risk of AAA events by at least 25%, 616 primary outcome events will be required (power 90%, alpha 0.05).

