## Introduction

### Background and rationale {6a}

Abdominal aortic aneurysm (AAA) rupture is an important cause of death in older adults [1]. Most AAAs are identified by incidental imaging or screening when they are small, asymptomatic and at low risk of rupture [2]. Up to 70% of small asymptomatic AAAs expand in size over time to ≥55 mm when the risk of rupture increases [2, 3]. The only established way to prevent AAA rupture is elective repair by open or endovascular surgery [4, 5]. Randomised controlled trials have shown that elective surgical repair of small (< 55 mm) asymptomatic AAAs does not reduce mortality [6]. Clinical guidelines recommend that small (< 50 mm in women and < 55 mm in men) asymptomatic AAAs are managed conservatively by repeat imaging surveillance until they reach threshold diameter when surgical repair should be considered [4, 5]. Since most non-surgically managed AAAs continue to grow in size until they reach the threshold for surgical repair, there is an unmet need to identify drug therapies able to limit AAA progression [2].

Previous randomised clinical trials have tested the efficacy of blood pressure-lowering agents [7–10], antibiotics [11–16], the mast cell inhibitor pemirolast [17], the anti-platelet inhibitor ticagrelor [18] and the fibrate fenofibrate [19], to slow AAA growth [20]. None of these trials has demonstrated a benefit of tested medications in limiting AAA growth. Important limitations of these past trials have included small sample sizes, short follow-up and a focus on imaging findings rather than clinically important outcomes [20–22].

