### Outcomes {12}

#### Primary outcome

The primary assessment will compare the number of AAA events (defined as the occurrence of AAA repair or AAA mortality due to rupture) between study groups which were observed during the treatment period. This will be in the form of an intention to treat (ITT) comparison including all randomised participants.

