#### Secondary outcomes

Secondary assessments will involve ITT comparisons including all randomised participants to test the effect of metformin versus placebo on the following outcomes:
i*AAA growth assessed by ultrasound*: Current clinical guidelines in every participating country recommend patients with ≥35 mm AAA undergo ultrasound imaging surveillance as part of their standard clinical care [5, 37, 38], which will be used to determine AAA growth over the course of the study. Digital Imaging and Communications in Medicine (DICOM®) AAA ultrasound images will be transferred from participating sites to the coordinating centre at screening and thereafter. The maximum anteroposterior orthogonal outer wall-to-outer wall measurement will be centrally assessed by experienced observers who have previously been shown to have excellent imaging analysis reproducibility. If DICOM images are not available, the maximum anteroposterior orthogonal outer wall-to-outer wall measurement will be measured by a site investigator experienced in reading ultrasound. Linear mixed effects modelling will be used to analyse AAA growth as previously described [39, 40]. If participants undergo imaging by other or additional modalities as part of clinical care, such as CT and/or magnetic resonance imaging, these images will also be collected and used to assess AAA diameter and volume growth independent of ultrasound imaging. If data becomes available from these differing imaging modalities on a sufficient sample of participants, a meta-analysis of the different data sets will be performed.ii*MACE*: Defined as non-fatal myocardial infarction, non-fatal stroke and cardiovascular death (i.e. sudden death, death due to myocardial infarction, valvular heart disease, cardiomyopathy or primary arrhythmia, or other cardiovascular disease or investigations or procedures related to these presentations).iii*Health-related quality of life*: Health-related quality of life will be assessed by generic (short form 36; SF-36) and disease-specific (the Aneurysm-Dependent Quality of Life [AneurysmDQoL]). These assessments will be performed at entry and annually.iv*Requirement for the peripheral vascular surgical procedure*: Defined as lower limb peripheral revascularisation (open or endovascular), carotid artery revascularisation, other aneurysm repair and major amputation. Incidence of the composite event (i.e. first occurrence of any procedure) and total number of events will be examinedv*All-cause mortality* is defined as death from any cause.

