#### Health economic assessments

If a significant effect of metformin on the primary outcome is observed, cost-effectiveness and cost-utility analyses will be performed. These evaluations will adopt a health system perspective, including estimates of all healthcare costs, particularly those relating to drugs, doctors’ visits and in-patient charges and costed using standard country-specific list prices. The cost-effectiveness analysis will produce an incremental cost-effectiveness ratio defined as a cost per AAA event avoided. For the cost-utility analysis, health utility scores will be generated for each participant by converting responses to the SF-36 into a single SF-6D score using validated algorithms and applying country-specific utility weights where available; weights currently exist for the UK and Australia. Each year participants will be asked how many outpatient appointments they have attended, and specifically how many of those appointments were related to their AAA. These analyses will generate costs per quality-adjusted life year (QALY) gained (or lost) and include sensitivity analyses, particularly around using pooled or country-specific data for each cost-utility analysis. Country-specific thresholds for determining cost-effectiveness will be used where available and presented in combination with cost-effectiveness acceptability curves.

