### Adjudication

An independent adjudication committee, blinded to study treatment assignment, will adjudicate all potential primary outcome events as well as myocardial infarction, stroke and all-cause mortality.

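### Plotting the risk of AAA events by Kaplan-Meier, with other deaths presumably censored, would modestly overstate absolute risk in each arm; cumulative incidence should be shown instead

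*Protocol article*

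**What the plan says.** The Primary outcome section counts AAA events, "defined as the occurrence of AAA repair or AAA mortality due to rupture". Under Statistical methods for primary and secondary outcomes {20a}, the hazard ratio and its 95% confidence interval "will be calculated using the Cox proportional hazard analysis", and "event risk will be plotted on a Kaplan-Meier graph". The protocol does not say how deaths from other causes enter either analysis, and it mentions no cumulative incidence method.

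Other deaths are recorded. All-cause mortality, which "is defined as death from any cause", is a secondary outcome, and cause-specific mortality is exploratory. The blinded committee reviews potential primary events "as well as myocardial infarction, stroke and all-cause mortality" (Adjudication). If the primary result is significant, Health economic assessments plans an incremental ratio expressed as "cost per AAA event avoided".

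**The concern.** A participant who dies of a heart attack or cancer can no longer have a repair or a rupture death. Kaplan-Meier, used in the ordinary way, censors that death as though the participant could still have the event later. The resulting curve estimates risk in a hypothetical setting without other deaths. It is not the proportion of participants who will actually have an AAA event, which is how a curve labelled as event risk will be read.

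At stake is the absolute scale: the height of the curves, the gap between them, and anything computed from that gap. The gap is the denominator of both the number needed to treat and the cost per event avoided. A gap that is too wide therefore makes both figures too low, that is, too favourable to metformin.

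**Working it through.** **Inputs**
- Control event rate 9% per year (Sample size {14}), used as a constant hazard λ = 0.09.
- A 25% reduction (same section), so λ = 0.75 × 0.09 = 0.0675 on metformin.
- Horizon T = 3.5 years, the planned mean follow-up. T = 5 years is added because recruitment runs from November 2020 to December 2025 (Trial status) and the trial is event-driven, so participants who enter early can pass 5 years.
- Hazard of non-AAA death, m. The protocol gives none. I assume 2% to 6% per year, equal in both arms to begin with.

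**The plan's own figure.** The 31% over 3.5 years is the simple product 0.09 × 3.5 = 0.315. As a constant hazard, the same 9% gives 1 − exp(−0.315) = 27.0%. The comparison below uses the hazard form throughout.

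**Formulas**
- One minus Kaplan-Meier: 1 − exp(−λT), whatever the value of m.
- Cumulative incidence: λ/(λ + m) × [1 − exp(−(λ + m)T)].

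**Worked case, m = 0.04, T = 3.5**
- Control: 0.09/0.13 × [1 − exp(−0.455)] = 0.6923 × 0.3656 = 25.3%, against 27.0% by Kaplan-Meier.
- Metformin: 0.0675/0.1075 × [1 − exp(−0.37625)] = 0.6279 × 0.3136 = 19.7%, against 21.0%.
- Difference: 5.62 points, against 5.98. Number needed to treat: 17.8, against 16.7.

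**Range at 3.5 years** (Kaplan-Meier: 27.0% v 21.0%, difference 5.98 points, NNT 16.7)

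| Other death per year | Cumulative incidence, control v metformin | Difference (points) | NNT | Control risk overstated by | Difference overstated by |
|---|---|---|---|---|---|
| 2% | 26.1% v 20.4% | 5.79 | 17.3 | 0.9 points (3%) | 0.2 points (3%) |
| 4% | 25.3% v 19.7% | 5.62 | 17.8 | 1.7 points (7%) | 0.4 points (6%) |
| 6% | 24.5% v 19.1% | 5.45 | 18.4 | 2.5 points (10%) | 0.5 points (10%) |

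**At 5 years**, Kaplan-Meier gives 36.2% in controls. Cumulative incidence is 34.6%, 33.1% and 31.7% for other death of 2%, 4% and 6% per year, a relative overstatement of about 5% to 15%. The difference between arms is overstated by 4% to 13%.

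**Sensitivity to the event rate.** With the 12% per year that the protocol quotes from its registry, the relative overstatement at 3.5 years is much the same: 3% to 10% for the risk and 3% to 9% for the difference.

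**Unequal other-death rates, T = 3.5, placebo at 4% per year**
- Metformin at 2% per year: the cumulative incidence difference is 25.3 − 20.4, or 4.96 points before rounding. Kaplan-Meier still shows 5.98 and overstates it by about 1.0 point.
- Metformin at 6% per year: the difference is 25.3 − 19.1, or 6.25 points before rounding. Kaplan-Meier now understates it by about 0.3 points.

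The Kaplan-Meier curves are the same in both cases, so they cannot show which one applies.

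**The case against.** Several objections have force.

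- **The primary inference is sound.** A reader might infer that the trial's main result is biased. It is not. With other deaths censored, the Cox model estimates a cause-specific hazard ratio, which is a valid measure and test of the effect on the rate of AAA events. This stands in full.
- **The size rests on an assumption.** A reader might infer that non-AAA death is known to be substantial here. The protocol gives no death rate and no expected age. Entry is from age 18, and the remark in the background that AAA "rupture is an important cause of death in older adults" is about rupture deaths in general. The direction for each arm's risk holds for any rate above zero; the size does not come from the document.
- **Benefit is not always overstated.** That conclusion needs similar other-death rates in the two arms. The last check above shows the sign reversing when they differ.
- **No absolute measure is planned from the curves.** The protocol names no risk difference or number needed to treat, and does not say how events avoided will be counted for the economic analysis, which is itself conditional on a significant primary result.
- **Other deaths will be compared between arms anyway**, through the all-cause and cause-specific mortality outcomes. This helps a reader interpret the hazard ratio but does not correct the curves.
- **Detail is deferred.** The methods section calls itself brief and points to a later analysis plan, which may add cumulative incidence. This lowers the severity. It does not remove the point, because the protocol already names the estimator and describes its output as event risk.

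**Conclusion.** The point holds as a minor reporting correction. If deaths from other causes are censored, the planned curve overstates the actual risk of an AAA event in each arm. Under constant hazards, 9% per year of AAA events and an assumed 2% to 6% per year of other death, control risk is too high by 0.9 to 2.5 points at 3.5 years. Only with equal other-death rates in the two arms does it follow that the risk difference is inflated, by 0.2 to 0.5 points on roughly 6, and that a number needed to treat or cost per event avoided taken from the curves would be too low. The documents do not support a stronger reading, whether that the hazard ratio is wrong, that absolute benefit must be exaggerated, or that non-AAA mortality is known to be high.

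**What to change.** In the protocol or the analysis plan, before unblinding:

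- Plot and tabulate Aalen-Johansen cumulative incidence of AAA events by arm, with death not due to rupture as the competing event.
- Take any absolute risk difference, number needed to treat or count of events avoided from those estimates, including for the economic analysis.
- Keep the cause-specific Cox hazard ratio as the primary effect measure, state that deaths from other causes are censored in it, and report the hazard ratio for non-AAA death beside it.

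The cost is a change of wording and one extra analysis. No new data are needed, since deaths and potential primary events already go to blinded adjudication. The displayed risks will be slightly lower than Kaplan-Meier would show.
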